### Study procedures

#### Screening visit

TEMPUS-FUGIT starts with a screening visit, where study procedures will be explained, eligibility criteria will be checked and informed consent will be obtained by one of the researchers. If the participant qualifies for the study, weight (SECA, model no 8801321009, SECA UK Ltd.) will be measured to the nearest 0.1 kg and height (Harpenden stadiometer Holtain Ltd., Crosswell UK) to the nearest 0.1 cm, measured barefoot, standing upright with clothes on. BMI is calculated through weight/height^2^ (kg/m^2^). Hand grip strength (HGS) will be measured with a handheld dynamometer (Jamar 1, TEC Inc., Clifton, NJ, USA) while the participant is seated, holding the arm in a 90° angle. According to the Southampton protocol, HGS is measured six times for alternating hands and the maximal value is reported [32, 33]. The chair stand test (CST) determines leg muscle strength by measuring the time it takes for the participant to rise five successive times out of a chair as fast as possible without using any support and holding the arms crossed in front of the chest. Cut-off values for low muscle strength according to EWGSOP2 (and, hence, probable sarcopenia) are > 15 s for the CST for both sexes and a HGS < 27 kg and < 16 kg for men and women respectively [5]. Finally, when no recent lab results (12 weeks old) are available, an additional fasted sample will be taken in order to check whether the participants fasted glucose levels are < 126 mg/dl or HbA1C < 6.5%, to exclude diabetes mellitus [34].

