### Outcome measurements

For the cross-sectional phase, outcome measurements will be taken at the baseline test visit.The primary outcomes in this phase are:Differences in multiple GM α-, and β-diversity indices, enterotypes, bacterial cell counts and abundance of specific taxa between sarcopenic older adults and non-sarcopenic controls using two fecal samples collected in each group at the baseline test visit [52, 53]. Both GM diversity indices and measures for expression of bacterial abundance will be specified in the section “Assessment of GM composition and statistical analyses” further below.Differences in the levels of the intestinal inflammatory markers fecal calprotectin, lactoferrin and S100A12 between sarcopenic older adults and non-sarcopenic controls using two fecal samples collected in each group at the baseline test visit.Secondary outcomes assessed in sarcopenic older adults are:Associations between GM composition and clinical parameters: 1) ALM (by whole body DXA and BIA), muscle strength (HGS, CST and knee strength) and physical performance (gait speed and SPPB); 2) protein intake by four-day food diaries and risk of malnutrition by the MNA-SF.Associations between GM and levels of systemic (hs-CRP; IL4, IL6, IL-13, IL-1β, TNF-α, and creatin kinase) and intestinal (fecal calprotectin, lactoferrin and S100A12) inflammatory markers.Associations between levels of systemic and intestinal inflammatory markers.Associations between fecal calprotectin, lactoferrin, S100 and respectively: 1) aforementioned systemic inflammatory markers; 2) ALM (whole-body DXA), muscle strength (HGS, CST, knee strength) and physical performance (gait speed, SPPB); 3) systemic muscle biomarkers (myostatin, activin A, irisin, apelin).

For the longitudinal phase in sarcopenic participants, outcome measurements will be collected from the baseline test visit until the week 12 visit. The primary outcome of this phase is:Change in GM composition between the protein intervention group (group B, Fig. 3) and the placebo group (group E).

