### Assessment of GM composition and statistical analyses

GM analyses will comprise determination of within sample diversity (α-diversity), including sample richness, taxa abundance, evenness, and taxa distribution through the following indices: Chao 1, Shannon and Simpson’s indices, abundance-based coverage estimators (ACE) index and the Good’s Coverage index. Taxa abundance will be expressed as Operational Taxonomic Units (OTU) and/or Amplicon Sequence Variants (ASV). Sequencing reads will be demultiplexed with LotuS (version 1.565) and processed further with the DADA2 pipeline (version 1.6.0), using the RDP classifier version 2.12 for taxonomy assignment (default parameters). Between sample dissimilarity (β-diversity) will be determined with Bray–Curtis dissimilarity (through a distance based non-parametrical permutational analysis of variance (PERMANOVA) test) and weighted and unweighted UniFrac (through principal coordinates analysis (PCoA)), respectively. Comparisons of relative GM abundance between sarcopenic and non-sarcopenic older adults will be performed through linear discriminant analysis (LDA) effect size (LEfSe). GM analyses, as well as visualization of the results will be performed using R vegan and phyloseq packages [54]. Enterotyping (or community-typing) will be performed based on the Dirichlet-multi-nominal Model (DMM) approach in R (dmn function) as previously described on a combined genus-level abundance matric containing the study samples as well as 1106 Flemish Gut Flora Project (FGFP) samples to increase accuracy [55, 56]. Continuous data will be checked for normality with the Shapiro–Wilk test. The t-test will be performed for between-group analysis of continuous clinical parameters, if normally distributed. For GM analyses, non-parametric testing will be applied. The Mann–Whitney U test will be performed in case of non-parametric distribution. Correlations between microbiota species and clinical parameters will be assessed with Spearman correlation. Linear regression models adjusted for putative confounders (e.g., age) will be used to check for associations between GM species abundance and clinical parameters. To determine possible effects of the interventions on GM in different groups, linear mixed models will be applied. Multiple testing corrections will be applied if it is applicable (Benjamini-Hochberg- False Discovery Rate (FDR)). An FDR of ≤ 0.10 will be taken into account for GM analyses [57]. Level of significance will be a p-value of ≤ 0.05. A bioinformatician from VIB and a statistician from LBiostat will be consulted for the statistical analyses.

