
### Sample size

In TEMPUS-FUGIT, a pragmatic sample of 100 sarcopenic people from the longitudinal phase, will be compared with 100 non-sarcopenic volunteers. Therefore, 110 non-sarcopenic controls will be recruited, in order to ensure 100 included control persons that, similarly to the sarcopenic participants, have a protein intake < 1.5 g/kg BW/day. Indeed, based on previous similar data, we expect, a drop-out of 5.88% in the non-sarcopenic control group due to a protein intake > 1.5 g/kg BW/day, [58]. Due to the exploratory character of this study, no sample size calculation was performed. Based on previous studies, 100 participants in each group is considered as sufficient for this study [16, 18, 29].

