## Discussion

TEMPUS-FUGIT aims to unravel the gut-muscle axis in sarcopenia by a two-fold set-up. First, cross-sectionally, by comparing GM composition and intestinal inflammation between sarcopenic and non-sarcopenic older adults. Second, in a longitudinal RCT set-up, by assessing the effects of combined, optimized, and individualized anabolic treatments for sarcopenia on GM and intestinal inflammation in sarcopenic older adults.

A first strength of TEMPUS-FUGIT is its well-considered design, defining sarcopenia according to the most recent criteria of the EWGSOP 2 [30]. Moreover, this study excludes participants with comorbidities influencing GM (e.g., malignancy, IBS, IBD or chronic kidney disease) and medications influencing muscle (e.g. corticoids or diabetes medications), resulting in an ideal population to explore the gut-muscle axis. Furthermore, this study aims to match both groups according to gender, age and BMI, since these factors influence both GM composition and sarcopenia [18, 60]. Thus, TEMPUS-FUGIT avoids bias related to these parameters, which was not always the case in previous studies investigating muscle mass, strength and GM in older adults [61–63].

Secondly, state-of the art metagenomic sequencing methods (e.g. Quantitative Microbiome Profiling, Shotgun whole genome sequencing) will be used to explore quantitative signals and bacterial functionality, which has not yet been done in an EWGSOP2-defined sarcopenic population [17].

Third, rather than solely comparing GM between non-sarcopenic and sarcopenic older individuals, TEMPUS-FUGIT pioneers in the assessment of intestinal inflammation markers, i.e., S100A12, fecal lactoferrin and fecal calprotectin, with the latter marker having a high specificity and sensitivity for gut inflammation [64]. This study will also investigate the possible associations between intestinal inflammation and respectively systemic inflammation and GM composition and its contribution to the development of sarcopenia, which has, to our knowledge, not yet been investigated.

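### The plain Spearman correlations of taxa with grip strength, knee strength and lean mass leave sex uncontrolled within the sarcopenic group

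*Protocol article*

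**What the plan says.** Four parts of the protocol article bear on this.

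- **Who and what.** In Outcome measurements, the list opens with "Secondary outcomes assessed in sarcopenic older adults are" and relates microbiota composition to "ALM (by whole body DXA and BIA), muscle strength (HGS, CST and knee strength) and physical performance (gait speed and SPPB". No height index or sex standardisation is given for any of these. Sample size puts the group at "a pragmatic sample of 100 sarcopenic people from the longitudinal phase".
- **How.** Assessment of GM composition and statistical analyses gives two methods in consecutive sentences: "Correlations between microbiota species and clinical parameters will be assessed with Spearman correlation", then "Linear regression models adjusted for putative confounders (e.g., age) will be used to check for associations between GM species abundance and clinical parameters". The first has no stratum and no covariate. The second gives age as its only example of a confounder.
- **Sex and strength.** The Screening visit section sets low strength at "a HGS < 27 kg and < 16 kg for men and women respectively", or a chair stand time of "> 15 s for the CST for both sexes".
- **Sex as a common cause.** The Discussion explains that "this study aims to match both groups according to gender, age and BMI, since these factors influence both GM composition and sarcopenia".

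Sex is controlled in two places: cases and controls are gender-matched (Participants), and randomisation is stratified by sex (Intervention period).

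**The concern.** The article identifies gender as acting on both sides of the association, then names a correlation that takes no account of it. Neither protection reaches this analysis. Matching balances sex between cases and controls, and stratified randomisation balances it between arms. A correlation computed among the cases alone still contains all the variation in sex within that group.

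On an absolute scale, grip, knee strength and lean mass tend to be higher in men. If a taxon also differs by sex, the pooled correlation is non-zero even when taxon and strength are unrelated among men and among women. Control of the false discovery rate does not help, because the pooled association is not a chance result: it exists, but through sex. The Abstract and the concluding Discussion expect the study to contribute microbial biomarkers of sarcopenia, and a sex-related taxon could enter that list as a muscle-related one.

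**Working it through.** The plan has no figure to reproduce here, since no sample size calculation was made. The check asks how often a taxon with no within-sex link to grip would be declared associated.

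**Inputs from the protocol article:** 100 sarcopenic participants; grip limits of 27 kg (men) and 16 kg (women); a sex-neutral chair stand route; significance at p ≤ 0.05.

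**Assumptions not in the documents:** source grip mean (SD) of 30 (7) kg in men and 19 (5) kg in women; 50% or 30% men; 0% to 90% entering by chair stand alone with grip above the limit; a sex difference d in the (log) taxon of 0 to 0.8 SD.

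**Step 1: expected spurious correlation.** Let p be the share of men, A_g the chance that a random man out-grips a random woman in the sample, and A_t the chance that his taxon value exceeds hers. With no within-sex link, the pooled Spearman correlation is approximately

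ρ ≈ 12 · p(1 − p) · (A_g − 0.5) · (A_t − 0.5), with A_t = Φ(d/√2).

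Simulated A_g was about 0.90 to 0.97. For d = 0.5, A_t = Φ(0.354) = 0.638.

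- 50% men, A_g = 0.97: 12 × 0.25 × 0.47 × 0.138 = 0.195.
- 30% men, A_g = 0.905: 12 × 0.21 × 0.405 × 0.138 = 0.141.

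At n = 100 the two-sided 5% critical value is about 1.984/√(98 + 1.984²) = 0.197. In the first case the expected spurious correlation lies almost on that limit, so about half of such trials would cross it.

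**Step 2: simulation (1,000 runs per setting).** Pooled Spearman compared with Spearman partialled on sex, selected settings:

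| Men | By chair stand alone | d (SD) | Mean pooled ρ | Pooled p ≤ 0.05 | Sex-partialled p ≤ 0.05 |
|---|---|---|---|---|---|
| 50% | 0% | 0 | 0.00 | 4.8% | 4.0% |
| 50% | 0% | 0.3 | 0.12 | 21.3% | 5.4% |
| 50% | 0% | 0.5 | 0.20 | 50.4% | 4.6% |
| 50% | 0% | 0.8 | 0.31 | 89.9% | 6.0% |
| 30% | 30% | 0 | 0.00 | 5.7% | 5.0% |
| 30% | 30% | 0.3 | 0.08 | 13.1% | 5.2% |
| 30% | 30% | 0.5 | 0.14 | 26.5% | 5.0% |
| 30% | 30% | 0.8 | 0.22 | 57.4% | 5.0% |

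The simulated mean correlations at d = 0.5 (0.199 and 0.136) agree with Step 1. Over all settings the pooled rates were about 13–21%, 27–51% and 57–90% for d = 0.3, 0.5 and 0.8. A separate set of runs with 30–50% men and 0–50% entering by chair stand alone gave about 13–22%, 26–51% and 55–87%, which is the same picture within simulation error. Sex-partialled rates were about 4–6% throughout.

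**Step 3: what drives it.** With d = 0 the pooled rate is near 5%, so the excess comes only from the sex difference in the taxon. It persists when 30–90% enter by chair stand alone, so it does not depend on everyone being selected on grip.

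**The case against.** The strongest reply is that the next sentence already plans an adjusted analysis of the same association. Its example of a confounder is not exhaustive, and the Discussion shows that the investigators regard gender as one. The Abstract names linear regression, not Spearman, for these cross-sectional associations. Covariate lists and scaling are commonly left to a statistical analysis plan, and a statistician is to be consulted. This stands in part: the regression leaves room for sex, and it would be wrong to say that the plan excludes it. But the Spearman analysis is a stated method, and an adjusted regression beside it does not correct the correlations that would be reported from it.

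Several stronger readings are tempting, and the documents do not support them.

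- *The entry limits force the sexes apart.* They are upper limits on the grip route only. The permitted ranges overlap below 16 kg, and the chair stand limit is the same for both sexes. Knee strength is not an entry criterion, and low lean mass is not required for probable sarcopenia. For those two measures any sex gap reflects body size, not selection.
- *Faecal markers are to be correlated with muscle by plain Spearman.* The Spearman sentence covers microbiota species. The only method stated for associations involving inflammatory markers is linear regression, in the Abstract, without covariates.
- *Every sex-related taxon will surface.* At a 0.3 SD difference most would not reach p ≤ 0.05. The documents give no sex difference for any taxon.

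It is also fair that the simulated rates are for single tests at 0.05, whereas the microbiota analyses apply a false discovery rate of 0.10. The percentages are therefore not the trial's declaration rates.

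**Conclusion.** The concern holds as a weakness of a stated secondary analysis. Plain Spearman over both sexes, applied within the sarcopenic group to grip, knee strength and lean mass, can present a sex-related taxon as muscle-related. For grip at n = 100, the single-test rate rises from about 5% to roughly 13–22%, 26–51% and 55–87% for sex differences of 0.3, 0.5 and 0.8 SD. These figures rest on assumed grip distributions, sex ratios, entry routes and taxon differences. They were computed for grip only; for knee strength and lean mass the argument is by direction, not size.

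That the men and women are pooled, and that the measures are unindexed, is read from what the article does not state. A reader might go further and infer that the biomarker results would simply be markers of sex. Nothing in the documents shows how many taxa differ by sex or by how much, so that does not follow. The sex-matched primary case-control comparison is untouched. The change is still worth making before analysis, because the article itself names gender as acting on both sides and the remedy is nearly free.

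**What to change.** In Assessment of GM composition and statistical analyses:

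1. For HGS, knee strength and ALM, replace plain Spearman with Spearman partialled on sex, or computed on ranks taken within sex.
2. Name sex beside age as a covariate in the linear regressions with these endpoints, including any regressions of faecal markers on muscle measures.

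Indexing ALM to height squared is optional; it has not been shown to be needed once sex is partialled out. The cost is a change of wording and one degree of freedom. No new data are needed, since sex is already used for matching and stratification.

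Suggested text: *Associations of microbiota species with grip strength, knee strength and appendicular lean mass will be assessed by Spearman correlation partialled on sex. Linear regression models with these endpoints, for microbiota and for faecal markers, will include age and sex.*

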
### Sample size

In TEMPUS-FUGIT, a pragmatic sample of 100 sarcopenic people from the longitudinal phase, will be compared with 100 non-sarcopenic volunteers. Therefore, 110 non-sarcopenic controls will be recruited, in order to ensure 100 included control persons that, similarly to the sarcopenic participants, have a protein intake < 1.5 g/kg BW/day. Indeed, based on previous similar data, we expect, a drop-out of 5.88% in the non-sarcopenic control group due to a protein intake > 1.5 g/kg BW/day, [58]. Due to the exploratory character of this study, no sample size calculation was performed. Based on previous studies, 100 participants in each group is considered as sufficient for this study [16, 18, 29].

### Protocol amendment

The first version of the protocol dates from July 7^th^ 2021 and was accepted was to the Ethics Committee of UZ/KU Leuven on July 14^th^ 2021. Modifications to the protocol possibly impacting the study conduct, patient benefits and/or patient safety, changes of study aims, changes of study design, sample size, patient population and study procedures will require an amendment. Any amendment will be approved by the local Ethics Committee (EC) and will be agreed upon by the study team.

### Ethics and dissemination

TEMPUS-FUGIT was approved by the Ethical Committee (S65127) and registered at Clinical Trials.gov (NCT05008770). The researchers obtain written informed consent from each individual willing to participate in the study, according to good clinical practice. With this study protocol, a thorough overview is given of the methodology of the TEMPUS-FUGIT project, based on the Standard Protocol Items, Recommendations for Interventional Trails (SPIRIT) guidelines [59].

Dissemination of the results will take place through publications in scientific and professional journals and by international conferences. Adverse events will be registered by the study coordinator. The study coordinator monitors all data and reports to the principal investigator. All study-related data will be handled and stored confidentially under supervision of the study coordinator. Protocol amendments will be reported on ClinicalTrails.gov. The study is performed an accordance with the principles of the Declaration of Helsinki.

## Discussion

TEMPUS-FUGIT aims to unravel the gut-muscle axis in sarcopenia by a two-fold set-up. First, cross-sectionally, by comparing GM composition and intestinal inflammation between sarcopenic and non-sarcopenic older adults. Second, in a longitudinal RCT set-up, by assessing the effects of combined, optimized, and individualized anabolic treatments for sarcopenia on GM and intestinal inflammation in sarcopenic older adults.

A first strength of TEMPUS-FUGIT is its well-considered design, defining sarcopenia according to the most recent criteria of the EWGSOP 2 [30]. Moreover, this study excludes participants with comorbidities influencing GM (e.g., malignancy, IBS, IBD or chronic kidney disease) and medications influencing muscle (e.g. corticoids or diabetes medications), resulting in an ideal population to explore the gut-muscle axis. Furthermore, this study aims to match both groups according to gender, age and BMI, since these factors influence both GM composition and sarcopenia [18, 60]. Thus, TEMPUS-FUGIT avoids bias related to these parameters, which was not always the case in previous studies investigating muscle mass, strength and GM in older adults [61–63].

Secondly, state-of the art metagenomic sequencing methods (e.g. Quantitative Microbiome Profiling, Shotgun whole genome sequencing) will be used to explore quantitative signals and bacterial functionality, which has not yet been done in an EWGSOP2-defined sarcopenic population [17].

Third, rather than solely comparing GM between non-sarcopenic and sarcopenic older individuals, TEMPUS-FUGIT pioneers in the assessment of intestinal inflammation markers, i.e., S100A12, fecal lactoferrin and fecal calprotectin, with the latter marker having a high specificity and sensitivity for gut inflammation [64]. This study will also investigate the possible associations between intestinal inflammation and respectively systemic inflammation and GM composition and its contribution to the development of sarcopenia, which has, to our knowledge, not yet been investigated.

Fourth, in the longitudinal phase, the effect of single and combined, optimized, and individualized anabolic interventions on GM and intestinal inflammation will be assessed in a well-defined sarcopenic population. To the best of our knowledge, this has not yet been done in community-dwelling older adults with sarcopenia. Optimization and individualization of interventions were based on the state-of the art literature and the RCT design allows to assess causality. Also, dietary intake will be registered through detailed food diaries. Physical activity will be reported in movement diaries as well as objectively measured with the IMU, allowing to account for incompliance to the interventions [16, 64].

Finally, the protein placebo compound administered in this study phase, is digestible maltodextrin (Resource Instant protein, Nestlé). This form of maltodextrin is completely digested before reaching the colon, therefore, not fermenting colon bacteria and not exerting a prebiotic effect, thus avoiding bias and making it a suitable placebo [65]. Unlike this study, previous studies using maltodextrin placebo have insufficiently clarified whether the digestible form is used or not [66].

Some limitations need to be taken into account. First, due to the exploratory character of this study, no power calculations for sample size were conducted. However, previous cross-sectional and case–control studies with sample sizes varying between 17–60 participants per group, reported significant results investigating the GM and muscle in older or sarcopenic adults [18, 67]. Therefore, in TEMPUS-FUGIT, the preset 100 participants in each group should be sufficient to detect significant differences in GM between both groups [16, 18, 68].

Second, due to the single center set-up, TEMPUS-FUGIT might be prone to selection bias. It has been shown that GM composition is influenced by geographic location, population demographics, ethnicity and the ‘exposome’, defined as “the measure of all the exposures of an individual from all sources, including environmental and occupational sources, in a lifetime and how those exposures relate to health” [64, 69, 70]. Hence, caution should be urged to extrapolate findings to the general population.

In conclusion, this study pioneers in its two-fold set-up aiming to further unravel the gut-muscle axis in sarcopenia. This study may open perspectives for research with microbial compounds such as pre-, pro- and symbiotics, targeting a sarcopenia-associated microbial landscape, as an additional treatment option for sarcopenia. We also expect this study to contribute to the discovery of new biomarkers, both clinical and microbial, for sarcopenia, which will help to identify persons at risk of this progressive muscle disease.

